**Fig. 1 Fig1:**
[figure not shown]
SPIRIT flow diagram. Schedule of enrolment, interventions, and assessments. * Participants are randomised after completion of the baseline assessment. **Suicide attempters only. *** Participants allocated to ASSIP-OA only

### Retention

Participants will always receive a scheduled appointment for an ASSIP-OA session in writing, either by mail, text message, or directly handed to them. The research team will remind participants of scheduled times to administer questionnaires by phone. Each participating centre will have a designated contact person available to address questions about the study or the recruitment process. Additionally, the research team will make regular visits to participating centres to provide support, answer questions, and reinforce awareness of the trial among healthcare staff.

### Data management

All quantitative data will be managed by Research electronic data capture (REDCap) an electronic software solution [28] that will be used for data collection and randomisation in the planned study. As REDCap is used for data monitoring, and given that this is a very brief intervention, consistent with other ASSIP trials, it does not warrant extensive oversight, and a Data Monitoring Committee (DMC) is thus not required. Qualitative data will be audio-recorded and transcribed in by a professional. All data will be kept in in fire-safe locked cabinets at the research unit to ensure participant confidentiality, and the code key will be stored separately. All data will be presented at group level so that no individual can be identified. All members of the research theme are educated and will adhere to the principes of Good Clinical Practice (GCP).

### Data analysis

We will use an intention-to-treat analysis. The primary outcome will be analysed using chi-square analyses. The secondary outcomes will be analysed using a so-called “mixed effect model approach” with the aim of examining changes before and after treatment as well as during the follow-ups. This approach can take into account data clustering and covariates as well as possible dropouts.

We will examine effects both between and within groups, to be able to determine if the preventive intervention ASSIP-OA in addition to TAU has a better effect than the control group, treatment as usual (TAU), after the intervention (between-group effect). Further, we want to find out whether ASSIP-OA and the control group have improved over time (within-group effect) and, if the ASSIP-OA has any effect, whether such effect is “driven” by the ASSIP-OA (interaction effect). The statistical approach is based on regression analyses. Contrary to more traditional variable-oriented analyses for repeated measurements, it has the benefit of taking into consideration the fact that data are not independent at repeated measurements over time and provides better handling of missing data by incorporating all available information. This method is now regarded as preferable to using more traditional methods for missing data in clinical studies.

For qualitative data collected through individual and focus group interviews, transcribed interviews will be analysed, and themes and subthemes will be identified and categorised following Braun and Clarke’s thematic analysis [51].

### Ethics

Ethical approval for the planned trial was granted by the Swedish Ethical Review Authority (2024-07392-01). The study therapists will continuously evaluate the participants’ suicidal ideation/planning at each treatment session. Any indication of increased suicidal ideation at any point during the project will prompt immediate contact with the participant’s care professionals. The participant’s physician will be informed without delay if a clinically relevant rise in suicidal ideation or other signs of acute distress are noted during the study. Adverse events will be registered at each session. Participation will be entirely voluntary, with no financial or other incentives, and all participants must provide written informed consent. In line with our ethical approval, patient insurance coverage is ensured and available to participants should the need arise.

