## Objectives and hypothesis

This paper outlines the study protocol for our upcoming study, which aims to evaluate a modified version of the Attempted Suicide Short Intervention Program (ASSIP), specifically for older adults (65+), the ASSIP for older adults (ASSIP-OA), as an add-on to usual treatment. The efficacy of the ASSIP-OA intervention will be evaluated by comparing it to a control group receiving only treatment as usual (TAU).

The main hypothesis is that participants randomised to the add-on treatment condition - the ASSIP-OA intervention - will experience a preventive effect on suicide and suicide attempts within 6, 12, and 24 months following the index episode. Also, we anticipate participants in the experimental condition to show better improvement in psychiatric symptoms/severity of suicidal ideation/coping skills/quality of life (secondary outcomes). Additionally, we aim to investigate if the brief preventive intervention (ASSIP-OA) is feasible, based on its acceptability, appropriateness, deliverability and fidelity, and whether participants have fewer days of inpatient care or experience any negative side effects. Further, the study also includes a qualitative approach to explore what kind of challenges and opportunities (a) older adults and (b) ASSIP-OA therapists experience in relation to implementing the brief preventive intervention, and if the modifications that we made in ASSIP-OA are relevant for older adults.

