## Methods

### Study setting and design

This study is designed as a multicentre two-group parallel randomised controlled trial (RCT), to be conducted within psychiatric services in the Swedish regions of Västra Götaland, Skåne, and Halland. Several additional regions have shown interest and may be added. Participants are randomly assigned to either:

a brief 3–5 session preventive intervention (approx. 1 session per week), the Attempted Suicide Short Intervention Program for Older Adults (ASSIP-OA), which is an add-on to usual treatment.a control group receiving treatment as usual (TAU) only.

Measurements will be taken prior to randomisation and after the last session (or after 5 weeks for the control group) and follow-up measurements (see below) will be assessed at 6, 12 and 24 months after the last session. An overview of data to be collected at the various timepoints is shown in Fig. 1. Following the baseline measurement, randomisation will take place electronically via REDCap (Research Electronic Data Capture) [28] and will be conducted using block randomisation with varying block sizes and with an allocation ratio of 1:1 between intervention groups. The randomisation procedure was designed by a statistician at the University of Gothenburg, independent of the research group. Randomisation will be blinded to the data processors, as well as to the researchers and clinicians conducting the initial assessments and screening (prior to randomisation). The size of the randomisation blocks will remain undisclosed. Due to the design of the intervention, blinding participants to their assigned group will not be possible. As it is anticipated that usual treatment will vary somewhat between the study locations, it will be mapped for each patient. Data on clinical diagnoses, healthcare contacts and treatments for mental health concerns during 24 months before and after baseline measurements are derived from medical records.

The study will follow the CONSORT guidelines and was pre-registered at Clinical Trial.gov NCT06831942 on February 21, 2025 and revised May 21, 2025. The present study protocol follows the recommendations for clinical trial protocols from the SPIRIT Declaration [29, 30], see Supplementary material 1 for checklist.

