#### Negative effects

Further, the Negative Effects Questionnaire (NEQ) [50], will be applied after the last ASSIP-OA session to answer the research question on side effects. NEQ contains of 32 items that are scored on a five-point Likert-scale (0–4) and differentiates between negative effects that are attributed to treatment and those possibly caused by other circumstances. At the end of the questionnaire there is also one open-ended question: “Describe in your own words if any other negative events or effects occurred, and what characterised them.”

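### Adverse-event registration and the NEQ are described only around ASSIP-OA sessions, so general adverse events cannot be compared with TAU

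*Protocol article*

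**What the plan says.** The only rule for collecting adverse events is one sentence in the Ethics section: "Adverse events will be registered at each session". Shortly before it, the same paragraph says "The study therapists will continuously evaluate the participants’ suicidal ideation/planning at each treatment session", which indicates whose sessions are meant.

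The Negative effects section says that the NEQ "will be applied after the last ASSIP-OA session to answer the research question on side effects", and that it "differentiates between negative effects that are attributed to treatment and those possibly caused by other circumstances". No timepoint for the control arm is given. The comparator, under Study setting and design, is "a control group receiving treatment as usual (TAU) only".

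The related aim, under Objectives and hypothesis, is to find out "whether participants have fewer days of inpatient care or experience any negative side effects". Data management describes REDCap as the monitoring tool, refers to the brevity of the intervention and to other ASSIP trials, "and a Data Monitoring Committee (DMC) is thus not required".

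**The concern.** Collection tied to an activity that exists in one arm produces data in that arm only. A death from another cause, a medical admission or an episode of acute distress could be recorded in an ASSIP-OA participant at a session. The same event in a TAU participant would have no described route into the adverse-event data. If the two arms were later set side by side, ASSIP-OA would show the excess even with equal true rates. If they were not, the trial would have no background rate for an older population with much physical and psychiatric illness.

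Distress is a foreseeable event here: the Interventions section reports, from clinical experience elsewhere, that some older men found the video playback difficult. An analysis plan cannot repair this later, because it can only use what was collected.

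**Working it through.** The point rests on reading the sections together. The plan states no figure for harms.

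**1. What counts as a session.** Study setting and design gives ASSIP-OA 3 to 5 sessions at about one a week. The first measurement after baseline follows the last session in that arm, but comes at 5 weeks for controls. Participants and recruitment separates an appointment with an ASSIP-OA therapist from the next research assessment. Retention separates ASSIP-OA sessions from the times at which questionnaires are given. Sessions are thus therapy contacts, and TAU participants have none.

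**2. Whether silence about controls is informative.** Under Secondary outcomes the article adds a 5-week control timepoint in so many words. The NEQ text has no such addition.

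**3. Harm-related data by arm, as described.**

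| Source (section) | ASSIP-OA | TAU |
|---|---|---|
| Adverse events (Ethics) | 3 to 5 sessions, plus any boosters | none described |
| NEQ (Negative effects) | once, after the final session | none described |
| Suicide attempts and suicide deaths (Primary outcome) | records and registers | same |
| Psychiatric hospitalisations and contacts (Health-care utilisation) | records, 12 and 24 months | same |
| Ideation, MADRS, GAD-7, EQ-5D-5L (Secondary outcomes) | baseline, post-treatment, 6, 12, 24 months | baseline, 5 weeks, 6, 12, 24 months |

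Only the first two rows are one-sided. The shared rows do not name non-suicide deaths, medical admissions, or distress that scales at fixed timepoints do not record.

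**4. The time after therapy.** Table 1 follows the last session with letters, and a booster session may be offered in a new crisis. Boosters are the only further sessions described, so neither arm has routine adverse-event registration up to 24 months.

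**5. What one-sided data can show (illustration).** If an event type is never seen in n ASSIP-OA participants, the one-sided 95% upper limit is 1 − 0.05^(1/n). That is 4.9% for n = 60 and 4.4% for n = 66, with no control rate beside it.

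**6. What two-sided data could show (illustration, assumed rates).** With n per arm, rates p1 and p2 and mean rate p, power = Φ{[|p1 − p2| − 1.96·√(2p(1−p)/n)] / √([p1(1−p1) + p2(1−p2)]/n)}.
- Check on the plan's own design: 30% against 10% with n = 60 gives (0.200 − 0.143)/0.0707 = 0.804, so power is 0.789, close to the stated 0.80.
- 5% against 15%: (0.100 − 0.107)/0.0540 = −0.136, power 0.45.
- 10% against 20%: (0.100 − 0.128)/0.0645 = −0.430, power 0.33.

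Symmetric collection would therefore give estimates with wide intervals and modest power for a 10-point difference. Its value is an unbiased contrast, which one-sided collection cannot give.

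**The case against.** Four objections deserve an answer.

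**Both arms supply the gravest harms.** A reader might infer that TAU has no harms data, or that no safety comparison is planned. The documents do not support either. The records and registers give suicide attempts, suicide deaths and psychiatric hospitalisations in both arms, the symptom scales are given in both, and Data analysis compares the primary and secondary outcomes between groups. This objection stands and limits the point to other adverse events.

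**The question on side effects names no comparator.** A reader might infer that it cannot be answered, or that harm from video playback is a stated research question. Neither follows. The inpatient-days half of the aim is comparative. The side-effects half is not, and the Discussion restates it next to feasibility. The NEQ asks for attribution, so it can answer descriptively within ASSIP-OA. This also stands. What remains is that no background rate is available.

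**The word only is inferred from silence.** Figure 1 is not shown, and its footnote marks some items as "Participants allocated to ASSIP-OA only" without our being able to see which. The article is condensed, and the full protocol may schedule adverse-event questions at research contacts. The Ethics section also requires care professionals to be contacted about rising ideation at any point, without restriction by arm. This stands as a caveat. The stated collection points are still specific, and both belong to one arm.

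**No adverse-event table by arm is announced.** True, so a spurious excess is a risk and not a planned result.

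Two further inferences go too far. The final session may mean the last one attended, so the handling of early stoppers is ambiguous and the text does not show that they are missed. The absence of a DMC is argued on several grounds and is not the fault raised here, although REDCap can monitor only what is entered.

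**Conclusion.** The concern holds in a limited form. As described, general adverse-event and NEQ data arise in ASSIP-OA only: 3 to 5 scheduled adverse-event points plus any boosters against none in TAU, and one NEQ against none. They cannot be compared between arms, and routine registration stops in both arms after the last session apart from boosters. Suicidal acts, psychiatric admissions and symptom change are not affected, nor is the primary analysis.

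This assumes that session means an ASSIP-OA therapy session, which the article's usage supports, and that neither Figure 1 nor the full protocol schedules adverse-event collection for controls, which cannot be checked here. The change is worth making early: recruitment is planned from June 2025 to 30 June 2029, and events that were not asked about cannot be fully recovered afterwards.

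**What to change.** - Ask the same adverse-event questions in both arms at the four research contacts that already exist: post-treatment (5 weeks for controls) and 6, 12 and 24 months.
- Extend the extraction from the registers and records already named to all-cause deaths and all admissions, in both arms.
- State that any between-arm comparison of harms uses these symmetric sources only.
- Report session-recorded events and the NEQ as descriptive within ASSIP-OA, and say so where the side-effects aim is stated.
- If Figure 1 or the full protocol already schedules adverse-event collection at research contacts in both arms, correct the Ethics sentence to match; nothing else in the collection schedule need change.

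The cost is a short form, somewhat wider data extraction and slightly more burden on participants at contacts that take place anyway. No new visits are needed. If the sponsor regards this as an important modification, the Trial status section requires an ethics application and an updated registration.

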## Discussion

Suicide rates remain high among our oldest citizens, but older adults are still gravely underrepresented in clinical suicide prevention research [52]. It is our hope that the development and evaluation of ASSIP-OA will help to mitigate this gap.

This multicentre preventive intervention study, conducted as an RCT, aims to evaluate a modified version of the ASSIP intervention as an add on to TAU specifically for older adults (65+). A major adaptation is that we will include also persons with a suicidal crisis requiring hospital care, as most older adults do not survive their first suicide attempt. Novel components of the older adult treatment program include; flexibility in treatment delivery, optional session together with one or two close relatives or other support person(s), and homework, letters, and case conceptualisation are adapted linguistically and content-wise to the target group. Additionally, we aim to investigate if the brief preventive intervention (ASSIP-OA) is feasible, based on its acceptability, appropriateness, deliverability and fidelity, and if participants experience any negative side effects. Further, in interviews with participants and focus groups with therapists we will identify challenges and opportunities that may arise in the implementation of a brief preventive intervention like ASSIP-OA.

Despite careful planning, the study has some limitations. First, we recognise that participant recruitment may be challenging. To address this, we have collaborated with participating centres to facilitate recruitment by providing training for therapists and medical staff responsible for screening, as well as engaging key contact persons who can monitor referrals to clinics and wards. Additionally, recruitment materials and contact information have been distributed to streamline the process. Second, the Swedish healthcare system differs from the context in which ASSIP was initially developed and evaluated. Access to psychotherapy in Sweden is much more limited, and almost non-existing for older adults, restricting opportunities to pursue long-term therapeutic goals identified by the intervention. To mitigate this discrepancy, we include only participants who have a designated healthcare physician responsible for their mental health. We also make efforts to contact the physician before and after the preventive intervention, sharing the case conceptualisation and advocating for its integration into the patient’s ongoing care plan.

If this suicide prevention intervention trial yields positive outcomes and proves feasible, the results could inform the development and implementation of a more person-centred care for suicidal older adults.

### Trial status

Protocol version 1 Registered Feb. 21, 2025, revised May 21, 2025. Recruitment is scheduled to begin in June 2025, and preliminary date for recruitment completion is 30 June, 2029. If there will be any important protocol modification, this will render an additional application to the Swedish ethical approval board and a modification of the trial registration.

## Data Availability

No datasets were generated or analysed during the current study.

## Abbreviations

ASSIP: Attempted Suicide Short Intervention Program
ASSIP-OA: Attempted Suicide Short Intervention Program for Older Adults
AUDIT: Alcohol Use Disorders Identification Test
Brief-COPE: Brief - Coping Orientation to Problems Experienced Inventory
CIRS-G: Cumulative Illness Rating Scale for Geriatrics
CONSORT: Consolidated Standards of Reporting Trials
C-SSRS: Columbia-Suicide Severity Rating Scale
DUDIT: Drug Use Disorders Identification Test
EQ-5D-5 L: EuroQol 5-Dimension 5-Level
GAD-7: Generalized Anxiety Disorder 7-item
GCP: Good Clinical Practice
MADRS-S: Montgomery-Åsberg Depression Rating Scale - Self report
MoCa: Montreal Cognitive Assessment
NEQ: Negative Effects Questionnaire
RCT: Randomised Controlled Trial
REDCap: Research Electronic Data Capture
SIS: Suicide Intent Scale
SPIRIT: Standard Protocol Items: Recommendations for Interventional Trials
TAU: Treatment As Usual
TMT: Trail Making Test
WAI-SR: Working Alliance Inventory - Short Revised
